## Abstract

**Background:**

Chronic constipation is a prevalent and often underestimated gastrointestinal disorder that significantly affects quality of life, particularly among women and older adults. In Spain, it is estimated to affect between 12% and 20% of the population, contributing to increased health care visits, economic costs, and medication dependency. Although pharmacological treatments such as laxatives are widely used, they often offer only temporary relief and may lead to adverse effects or dependency. There is growing interest in nonpharmacological interventions that address the root behavioral and functional causes of constipation, such as dietary habits, physical inactivity, and impaired defecation techniques. However, evidence regarding the effectiveness of such approaches, especially within a primary care setting, remains limited.

**Objective:**

This study aims to evaluate the effectiveness of a primary care–based structured rehabilitation program that combines behavioral reeducation and abdominal massage therapy in reducing the severity of chronic constipation and use of laxatives. A secondary aim is to assess improvements in quality of life and sustainability of effects over time.

**Methods:**

This is a randomized controlled trial involving adults aged 18 to 75 years from the counties of l’Anoia and Bages (Catalonia, Spain) who meet the Rome IV diagnostic criteria for chronic constipation. A total of 45 participants will be randomly assigned in a 1:1:1 ratio (approximately 22‐23 per center, with 15 per group overall) into 3 groups: a control group, behavioral intervention (BI) group, and behavioral intervention and massage (BIM) group. All participants will complete baseline assessments that include the Rome IV criteria, the Bristol Stool Form Scale, the CVE-20 quality of life questionnaire, and the International Physical Activity Questionnaire. The BI group will receive 2 group education sessions, focused on healthy bowel habits, diet, hydration, physical activity, stress management, and medication use, delivered by a multidisciplinary team. The BIM group will receive the same intervention as the BI group, plus two 30-minute sessions with a physiotherapist to learn abdominal self-massage techniques. The control group will receive usual care. Follow-up assessments will occur at 3 and 6 months after the intervention using the same instruments and a self-recorded calendar of laxative use and massage application. Data will be analyzed using appropriate statistical tests, including the *χ*^2^ test, a 2-tailed *t* test, and ANOVA/Kruskal-Wallis tests, depending on variable type.

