### Sample and Randomization

Calculations were based on published evidence suggesting that approximately 90% of patients in the control group would remain constipated at 3 months. We hypothesized that this proportion would decrease to 40% in the intervention groups (BI and BIM), corresponding to a 50% absolute difference. To detect this difference with 80% power and a 2-sided significance level of 5%, while allowing for a 10% dropout rate, 15 participants per group are required. With 3 groups, the total sample size will therefore be 45 participants in total. Recruitment will take place across the 2 participating centers (Anoia and Bages), with approximately 7 to 8 participants per group expected to be recruited at each center.

The sample will be selected (1) by means of a medical history review by nursing or medical personnel; if the health professional considers that the patient meets the criteria, they will refer the patient to the research physiotherapist; and (2) indirectly, by putting up posters in *casals cívics* (civic facilities) and pharmacies in the city. Anyone learning about the study this way can make an appointment with their health professional of reference (ie, nursing or medical staff) and discuss their interest in participating in the study. If the health care professional confirms that the patient meets the criteria, they will refer the patient to the research physiotherapist.

The randomization and allocation of patients will be performed by simple randomization using the specialized software RStudio (version 4.2.1; R Foundation for Statistical Computing). The distribution is expected to be homogeneous between groups. Randomization will be conducted by an independent researcher, and allocation will be concealed using sequentially numbered, opaque, sealed envelopes prepared in advance. This procedure ensures allocation concealment and minimizes selection bias.

The chosen sample size is based on feasibility and resource availability and is sufficient to detect large effect sizes. This study aims to assess the feasibility and potential impact of the intervention and to provide effect size estimates to guide future large-scale trials.

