### Intervention

#### BI Group

The behavioral education sessions are structured into two 60-minute workshops delivered in a progressive format. Session 1 focuses on understanding the physiology of defecation, the Rome IV diagnostic criteria, and bowel habits. Session 2 addresses lifestyle-related components, including dietary fiber and hydration guidelines, physical activity recommendations, stress management, optimal defecation posture, and the rational use of laxatives. The sessions are delivered by a multidisciplinary team (nurse, physician, physiotherapist, nutritionist, and psychologist) using multimedia presentations and printed handouts. Participants are encouraged to set personal bowel health goals. Questions and doubts raised during the first session will be discussed and resolved in the second session, ensuring continuity of learning and participant engagement.

The Bristol scale, Rome IV criteria, CVE-20 quality of life questionnaire, and International Physical Activity Questionnaire (IPAQ) [11,29-31] will be explained, and a calendar will be given to the patients to mark when they take any laxatives. Once the information sessions are complete, follow-ups will be scheduled 3 and 6 months later.

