### Statistical Analysis

The main variable will be the percentage of patients with constipation 3 and 6 months after the start of treatment for each group, a dichotomous qualitative variable. Prevalence will be estimated and analyzed using the *χ*^2^ test.

The other variables will be reported as percentages and counts for categorical variables and through mean, median, deviation, and quartiles for continuous variables. In order to analyze relationships between the main variable and the sociodemographic or other explanatory variables, the *χ*^2^ test will be used, and the relative risk will be estimated to compare the reduction between the two intervention groups with respect to the control group.

To evaluate the secondary variable, a continuous quantitative variable, ANOVA or the Kruskal-Wallis test will be used to determine differences between the 3 groups. To determine differences between pairs of groups, the Student *t* test or Mann-Whitney test will be used. Analyses will use 95% CIs, and the significance level will be set at 5%.

Due to the nature of the intervention, participant blinding is not feasible. However, to minimize potential bias in outcome assessment, data entry and statistical analysis will be performed by a researcher who is blinded to group allocation. This approach ensures objectivity in the interpretation of results, particularly for subjective outcome measures. All analyses will follow the intention-to-treat principle, including all randomized participants in the groups to which they were originally assigned. Missing data will be handled using multiple imputation under the assumption that data are missing at random. Statistical analysis will be performed with RStudio.

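### BI and BIM are taught in group workshops, but every named test treats participants as independent, so intervals against control may be too narrow

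*Protocol article*

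**What the plan says.** Patients are randomized individually. The Sample and Randomization section states: "The randomization and allocation of patients will be performed by simple randomization".

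The two active arms are taught in groups. The abstract says "The BI group will receive 2 group education sessions, focused on healthy bowel habits", and the BI Group section says "The behavioral education sessions are structured into two 60-minute workshops delivered in a progressive format". That section adds that questions raised in the first session are taken up in the second. The BIM Group section gives that arm the BI intervention plus two physiotherapist sessions on massage. The Control Group section provides usual care with no trial workshop.

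For the main variable, the Statistical Analysis section names the chi-square test and a relative risk for each intervention group against control. For the secondary variable, "ANOVA or the Kruskal-Wallis test will be used to determine differences between the 3 groups", with the Student t or Mann-Whitney test for pairs of groups. Intervals are at 95% and tests at 5%. Neither workshop nor center enters any of these analyses.

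**The concern.** Two arms are nested in workshops and one is not, so the design is partially nested. People who attend the same workshop share staff, content and discussion, and their outcomes may be more alike than those of people from different workshops. If so, the variance of a taught arm's mean or proportion is larger than the independent-data formula gives. Intervals against control are then too short and p values too small.

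The comparisons with control carry the trial's main conclusion. They also supply the effect sizes that the protocol wants for planning larger trials. BIM vs BI, which bears on the added value of massage, may be affected as well, depending on how the workshops are organized.

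**Working it through.** **Inputs from the protocol** (Sample and Randomization): "approximately 90% of patients in the control group would remain constipated at 3 months"; 40% in BI and BIM; "To detect this difference with 80% power and a 2-sided significance level of 5%, while allowing for a 10% dropout rate"; a stated size of 15 in each arm; about 7 to 8 participants per arm at each center.

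**Assumptions, not in the protocol:** ICC 0.01 to 0.10. The base case is one workshop per arm per center (sizes 8 and 7, mean m = 7.5). The protocol's 7 to 8 is a recruitment figure, not a workshop size, so other layouts are shown too.

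**Step 1. The plan's own figure.** Pooled two-proportion formula, two-sided 5%, 80% power, mean rate 0.65:

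n = [1.96 × √(2 × 0.65 × 0.35) + 0.842 × √(0.09 + 0.24)]² / 0.5² = (1.322 + 0.483)² / 0.25 = 13.04.

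Allowing for dropout, 13.04 / 0.9 = 14.5, which rounds up to 15. The stated size is reproduced, and it contains no allowance for clustering.

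**Step 2. Interval width against control.** The design effect is DE = 1 + (m − 1) × ICC and applies to the taught arm only. At 15 per arm, the half-width for the risk difference is 1.96 × √(0.09/15 + 0.24 × DE/15). With independence it is 1.96 × √(0.33/15) = 0.291.

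| Workshops per taught arm | ICC | DE | Half-width | Wider by |
|---|---|---|---|---|
| Two (m = 7.5) | 0.01 | 1.065 | 0.298 | 2% |
| Two (m = 7.5) | 0.05 | 1.325 | 0.323 | 11% |
| Two (m = 7.5) | 0.10 | 1.65 | 0.353 | 21% |
| Four (m = 3.75) | 0.01 to 0.10 | 1.03 to 1.28 | 0.294 to 0.318 | 1% to 10% |
| One of 15 | 0.01 to 0.10 | 1.14 to 2.40 | 0.305 to 0.413 | 5% to 42% |

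**Step 3. False-positive rate of the uncorrected chi-square test, taught arm vs control.** Exact calculation at 15 vs 15, with a binomial control arm and beta-binomial workshops of 8 and 7:

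| Common rate | ICC 0 | 0.01 | 0.05 | 0.10 |
|---|---|---|---|---|
| 90% | 2.5% | 2.7% | 3.6% | 4.7% |
| 70% | 5.5% | 5.9% | 7.5% | 9.6% |
| 65% | 5.2% | 5.6% | 7.3% | 9.4% |

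At 90% the discreteness of the small table keeps the test below 5% over this range. That protection depends on the layout: with one workshop of 15, the 90% figure reaches 7.0% at ICC 0.10, and with four workshops (4, 4, 4, 3) it is 3.4%. With a continuity correction and workshops of 8 and 7, the rate stays below 1% at 90% and is 1.7% to 3.7% at 65% to 70%. The protocol does not say whether a correction is used.

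**Step 4. Secondary t test, taught arm vs control.** Simulation with 40,000 runs and workshops of 8 and 7 gives 4.9% at ICC 0, then 5.3%, 6.8% and 9.0% at ICC 0.01, 0.05 and 0.10.

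**Step 5. BIM vs BI, if the arms attend separate workshops.** Uncorrected chi-square at a common rate of 65%, both arms in workshops of 8 and 7: 6.0%, 9.3% and 13.6% at ICC 0.01, 0.05 and 0.10. If the arms share workshops, the workshop effect is common to both and need not inflate this contrast.

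**The case against.** The strongest reply is that the size of the problem rests on quantities the protocol does not give. Two 60-minute sessions may induce very little correlation; at ICC 0.01 the t test against control gains less than one percentage point. Recruitment was spread over time, so workshops may have been smaller than 7 to 8. This stands, and it is why the point is conditional and shown as a range.

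A reader might infer more than the document supports in four ways:

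- **That every planned test exceeds 5%.** For the main variable at the protocol's own 90% rate, the chi-square test against control stays at 2.7% to 4.7% in the base case, and lower with a continuity correction.
- **That BIM vs BI is the worst affected contrast.** This requires separate workshops, which the protocol does not state.
- **That the trial is undersized.** The unpooled formula with the design effect on the taught arm gives 12.81 per arm at ICC 0.05 and m = 7.5. Allowing for dropout, 12.81 / 0.9 = 14.2, so 15 per arm still suffices on that formula. Enrollment has also closed. Sample size is not part of this point.
- **That correlation within workshops is certain.** No ICC is given, and none can be assumed as fact.

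It can also be said that a published article condenses the plan and that a clustering sensitivity analysis may sit in a statistical analysis plan not shown here. That is possible. But the article does fix the analyses, and all those it names assume independence. Nor does having few workshops justify the assumption: it makes an ICC hard to estimate from the trial, but it does not make the ICC zero.

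**Conclusion.** The concern holds in conditional form. Group teaching in two arms and none in the third, combined with independent-data tests, means that any positive within-workshop correlation makes the intervals against control too narrow. With workshops of 7 to 8 and ICC 0.01 to 0.10, the understatement of width is modest to moderate. The false-positive rate may exceed 5%, clearly so for the secondary t test at ICC 0.05 or above and for the uncorrected chi-square test when the common rate is near 65% to 70%. It does not do so at a common rate of 90% in the base layout. For BIM vs BI the answer waits on whether the arms share workshops. All sizes rest on the assumed ICC and workshop layout.

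**What to change.** Before analysis:

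1. Record the workshop attended by each BI and BIM participant.
2. State the number and size of the workshops, and whether BI and BIM share them.
3. Prespecify a sensitivity table that gives each contrast with the taught-arm variance multiplied by 1 + (m − 1) × ICC, at ICC 0.01, 0.05 and 0.10, using the actual workshop sizes. This needs no ICC estimated from the trial.
4. If the arms share workshops, compare BIM with BI within workshop.
5. Say in the conclusions whether each result holds across the range. No single assumed ICC should serve as a decision rule.

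The cost is one extra variable, one extra table and somewhat wider intervals. Data collection was expected to run to April 2026 and enrollment is complete, so the change affects only record-keeping and analysis.

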**Results:**

Participant enrollment concluded in August 2025, and data collection is ongoing and expected to continue until April 2026.

**Conclusions:**

This trial will provide evidence on the efficacy of conservative, low-risk interventions for managing chronic constipation in primary care. The findings may support broader implementation of integrative approaches that reduce pharmacological dependence and enhance patient empowerment, with potential public health and economic benefits.

## Introduction

Constipation is characterized by difficult or infrequent passage of stool, often accompanied by straining, pain, or a feeling of incomplete evacuation. It is one of the most common digestive problems in today’s society and contributes significantly to decreased quality of life, increased medical visits, and high costs to the health care system [1].

Constipation may be acute, usually lasting less than 6 weeks, or chronic, lasting more than 3 months. Most often, chronic constipation is the result of a primary disorder, that is, one caused by dietary factors (such as insufficient fiber intake), lifestyle factors (lack of mobility or a sedentary lifestyle), or a disorder causing deficient colonic propulsion or rectal emptying [2].

The prevalence of constipation differs across countries due to varying lifestyles and diet. On a global scale, it is between 10% and 15% [3]. According to the American Gastroenterological Association, the prevalence in the United States is approximately 16% in adults and 33% in people older than 60 years [4]. In Europe, it varies between 8% and 26% [5]. In East Asia, it has been reported that in China the prevalence of this pathology is 8.5% [6]. In the African pediatric population, it is 31.4% [7], with no data for the adult population. There is a lack of prevalence studies in South America, West Asia, and Africa.

The Fundación Española del Aparato Digestivo (Spanish Foundation of the Digestive System) estimates that constipation affects between 12% and 20% of the Spanish population [8]. On the other hand, Navarro-Ruiz et al [9], in a study conducted in the primary care setting in 2015, stated that it varied between 16% and 33% of the population.

An analysis of prevalence based on factors such as gender, age, physical activity level, and medication use in the population shows that constipation tends to be more frequent in women (at a 2:1 ratio), older people, people with low physical activity levels, and people taking medications with digestive side effects (eg, opioids, anticholinergics, and calcium channel blockers) [2-5,8-10]. Therefore, this condition is expected to increase in the coming years due to the prevalence of sedentary lifestyles and aging populations, especially in developed countries.

The diagnostic criteria for chronic constipation are the Rome IV criteria, shown in Textbox 1 [11]. Criteria must have been met for at least the last 3 months and symptoms must have started at least 6 months prior to diagnosis.

Textbox 1.Rome IV criteria for constipation.Two or more of the following criteria are met:Excessive straining in at least 25% of bowel movementsHard stools in at least 25% of the stools (Bristol type 1-2)Sensation of incomplete evacuation in at least 25% of bowel movementsSensation of anorectal obstruction or blockage in at least 25% of bowel movementsLess than 3 complete spontaneous bowel movements per weekThe presence of liquid stool is rare without the use of laxatives.Criteria are not met for the diagnosis of irritable bowel syndrome.

*Acute* constipation rarely causes complications or long-term health problems. Treatment is usually effective, especially if started promptly. However, long-term, chronic constipation is likely to pose a higher risk of complications [12] such as fecal incontinence [13], hemorrhoids (4%) [14], anal fissure (7.8%) [14], organ prolapse [15], fecal impaction [16] or stercoral perforation [17,18].

The current treatments available for this condition are limited: lifestyle modification, medication, and surgical intervention when the condition is severe [19-23]. Laxative treatment is effective, but there are often relapses after withdrawal, causing dependence in some patients. In addition, there are side effects such as electrolyte disorders, dehydration, and intestinal cramps [24]. Therefore, this condition calls for new multidisciplinary and conservative strategies, especially within primary care, that are accessible, low-risk, and empower patients in self-care.

There is growing evidence that abdominal massage can stimulate colonic motility, reduce transit time, and promote defecation through mechanical and neurophysiological mechanisms involving the enteric nervous system and visceral reflexes [25,26]. Behavioral reeducation, including guidance on bowel habits, posture, and toileting routines, has also been shown to improve constipation outcomes by targeting dysfunctional defecation behaviors and increasing patient awareness and adherence to lifestyle recommendations [27]. These approaches align with biopsychosocial models of gastrointestinal dysfunction, emphasizing nonpharmacological, patient-empowering strategies.

The primary objective of this study is to evaluate the effectiveness of a structured rehabilitation program based on behavioral reeducation and abdominal massage therapy in reducing the prevalence of chronic constipation and the use of laxatives at 3, 6, and 12 months after the intervention. The secondary objectives are to assess changes in quality of life among participants and to evaluate whether the observed effects are sustained over time.

## Methods

This protocol has been developed and drafted in accordance with the recommendations of the SPIRIT (Standard Protocol Items: Recommendations for Interventional Trials) guide [28].

### Design: Randomized Controlled Trial

This will be a randomized controlled trial with 3 groups: a control group, a behavioral intervention (BI) group, and a behavioral intervention and massage (BIM) group. The same number of people will be randomly distributed in each group with a 1:1:1 allocation ratio, so that the 3 groups are homogeneous for age, sex, and constipation characteristics. Data collection will be between 2024 and 2026.

### Scope: Primary Care

The choice of primary care as the study setting reflects its central role in the early management and long-term monitoring of chronic constipation. This environment ensures high feasibility, as the intervention can be delivered using existing staff—nurses, physiotherapists, general practitioners, and nutritionists—and infrastructure, requiring minimal additional resources. Moreover, the intervention is designed to be easily integrated into routine care pathways, aligning with preventive care goals and enhancing patient self-management strategies within the primary care framework.

### Population

This study will recruit patients aged 18 to 75 years assigned to the primary care centers of the counties of l’Anoia and Bages in Catalonia, Spain.

The inclusion criteria are having been diagnosed with primary constipation using the Rome IV criteria [11] lasting for more than 3 months and understanding Catalan, Spanish, or English.

The exclusion criteria are having constipation secondary to neurogenic, metabolic, endocrine, or postoperative diseases; having constipation secondary to medication for other pathologies, the medication list for which can be found in Multimedia Appendix 1; having any type of open abdominal and/or anal wound, such as a recent abdominal scar or anal fissure; meeting any absolute contraindication criteria for the use of abdominal massage therapy, such as an unstable fracture requiring absolute rest and immobilization, pregnancy, or active oncological procedures, and having a cognitive, psychiatric, or neurological condition that, in the clinical judgment of the health care professional, significantly limits the individual’s capacity to provide informed consent or to participate meaningfully in the intervention and data collection procedures.

